### 2.2. Study Design

This study is an RCT with a qualitative component and a waitlisted control group (Figure 1). This study is pragmatic in nature because it has been developed to evaluate the web-based program as it would typically be delivered. 

The 10-week web-based program will be administered by the administrating organization, Better Health Company (BHC), and is delivered during the year at primary school terms and midterms. In Australia, there are four school terms per year. The midterm programs will start approximately 6 weeks into the school term. Participants will be recruited for a school term or midterm program; a new recruitment cycle will begin, at the latest, 2 weeks prior to the commencement of the next earliest term or midterm program. Participants recruited during a school term or midterm recruitment cycle will only be considered for a school term or midterm program, respectively. Following study enrolment, participants allocated to the intervention group (Cohort 1) will complete the program in the subsequent commencing school term or midterm, whereas participants allocated to the control group (Cohort 2) will complete the waitlist control period in the next commencing school term or midterm. Participants allocated to the control group will not receive any intervention during the 10 weeks control period and will receive the (same) web-based program in the school term or midterm following the waitlist control term. Study involvement for each participant will run from baseline to 12-months post-program completion. 

Families who consent to the study will be randomized into the intervention or waitlisted control group. The randomization schedule was generated using block randomization (1:1 ratio) from Research Randomizer [41]. Group allocation will not be communicated to the BHC. Instead, study investigators will allocate participants to the respective school term or midterm in BHC’s data management system. In doing so, BHC’s health coaches, who are assigned to and have direct contact with families during the program, will be blinded to the study allocation.

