#### 2.3.2. Sample Size Estimation

The primary outcome will be the change in BMI z-score from baseline to 10 weeks. An a priori power analysis was conducted using G*Power version 3.1.9.4 [43] to estimate the sample size needed to detect a difference in the mean change in BMI z-score between the intervention and control group from baseline to 10 weeks using a *t*-test. The sample size estimation accounted for a possible reduction in BMI z-score within the control group, an effect size based on BHC’s pilot data, and a 30% attrition rate based on previous trials on a similar program (trials on the MEND program reported a 30% attrition) [44]. The effect size based on the change in BMI z-score and informed by pilot data was 0.6 (i.e., medium effect size using Cohen’s (1988) [45] criteria). With a 5% significance and 80% power, this study aims to recruit *n* = 118 participants (*n* = 59 intervention group; *n* = 59 control group) to observe a difference in the primary outcome measure between groups with this effect size using a *t*-test. 

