### 2.6. Outcome Measures

Outcome measures will be self-reported via surveys administered online, at baseline, post-program completion (10 weeks), and 6- and 12-months post-program completion. Participants allocated to the control group will be asked to complete an additional set of surveys following the 10 week control period. All study assessments will be administered online via a Research Electronic Data Capture (REDCap) [46,47] link, Australian Eating Survey (AES) [48], or Youth Activity Profile (YAP) [49] link, and distributed to participants via email.

Qualitative data will also be collected online through video conferencing and real-time transcribing platforms (Zoom [50], Otter.ai [51]) at 3 months post-program completion.

All study assessments, including study surveys and interviews, will be completed by both the participating child and parent/caregiver. All outcome measures will be self-reported by participants to complement the virtual nature of the intervention and include the participation of families from all geographic locations of Victoria. A study by Chai and colleagues supports the use of parent-reported measurements that are collected online for web-based lifestyle programs [52]. The study found that Australian parents of primary-school-aged children were relatively accurate in reporting their child’s anthropometric measurements, including their weight and height [52]. 

The primary outcome measure is the change in the child’s BMI z-score. Secondary outcomes include (the change in) the child’s BMI z-score, waist circumference, dietary intake, physical activity, quality of life, and the participating child and parent/caregiver’s experience of completing the program. Details on the collection of the outcome measures are summarized in Table 1.

The web-based program also includes surveys to be completed by participants as a part of the program activities. Data collected from these surveys may supplement data collected by study investigators, to inform outcome measures. 

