### 2.7. Data Analysis

All statistical analysis of quantitative data will be performed using IBM SPSS Statistics version 25 [46] and methods were confirmed with and reviewed by the Monash study statistician ([name]). 

The primary focus of this study is to test whether the web-based program has an effect on BMI z-score over a 10-week period. An independent *t*-test will be used to compare the difference in the mean change in BMI z-score between Cohort 1 and 2 from baseline to 10 weeks. Independent *t*-tests will also be used to compare the differences in the quantitative outcome measures between cohorts from baseline to 10 weeks. A 2 × 2 mixed ANOVA will be conducted to investigate the impact of the web-based program (between factor: web-based program vs. control) on BMI z-score from baseline to 10 weeks (within factor). Separately, mixed model ANOVAs will also investigate the impact of the web-based program on the secondary outcome measures (i.e., WC, diet quality score, physical activity score, and quality of life scores) from baseline to 10 weeks. The impact of being waitlisted (Cohort 2) will be explored to ascertain whether receiving the web-based program following 10 weeks of waiting will differ on the quantitative outcome measures from Cohort 1 over time. If being waitlisted does not have an impact on the quantitative outcome measures (as anticipated), a one-way repeated measures ANOVA will be used to assess the effect size of the web-based program on quantitative outcome measures overtime with greater certainty (i.e., power). Independent *t*-tests may also be used to compare the differences in the mean changes in quantitative outcome measures between cohorts or compare the mean differences in quantitative outcome measures for all participants at immediately pre-program (baseline or post-10-weeks waitlisted period) and post-program completion. 

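### The pooled one-way repeated-measures ANOVA would drop any child with a missing wave, at a planned 30% attrition; a linear mixed model would use every observed wave

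*Protocol article*

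**What the plan says.** All places are in the protocol article.

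- **Primary analysis (2.7).** The method is a two-sample t-test on change scores, which "will be used to compare the difference in the mean change in BMI z-score between Cohort 1 and 2 from baseline to 10 weeks". A second analysis of the same outcome, with two groups and two time points, is also planned: "mixed ANOVA will be conducted to investigate the impact of the web-based program (between factor: web-based program vs. control".
- **Pooled analysis (2.7).** If being waitlisted makes no difference, as the authors expect, "a one-way repeated measures ANOVA will be used to assess the effect size of the web-based program on quantitative outcome measures overtime". The section gives greater power as the reason. It does not list the waves that enter.
- **Attrition (2.3.2).** The sample size allows for "a 30% attrition rate based on previous trials on a similar program".
- **Waves (2.6).** Surveys are taken "at baseline, post-program completion (10 weeks), and 6- and 12-months post-program completion", with one extra set for controls after their waiting period.

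The software is SPSS. The article names no imputation method, no analysis population and no sensitivity analysis for missing outcomes. An analysis plan that is not shown may do so.

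**The concern.** The pooled ANOVA is chosen to gain power, but in its classical SPSS form it needs a value at every included wave. A child who answers three of four surveys contributes nothing. With substantial attrition planned and follow-up to 12 months, the method discards data that were collected. If children who leave differ on values already observed, the complete cases no longer represent those who started.

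The primary t-test has a related but smaller weakness. A change score needs both measurements, so a child without a 10-week value drops out, and the test makes no use of baseline to correct for who is missing. At stake are the credibility of the long-term results and, to a lesser degree, the 10-week contrast.

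**Working it through.** **1. The plan's own figure.** Inputs from 2.3.2: effect size 0.6, 5% significance (taken as two-sided), 80% power, 30% attrition. Input from 2.2: 1:1 allocation.

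- Normal approximation: n per arm = 2 × (1.96 + 0.84)² / 0.6² = 43.6, so 44. The exact noncentral t calculation gives 45 (power 80.4%).
- 45 × 1.3 = 58.5, so 59 per arm and 118 in total. This reproduces the stated target, so the target already treats dropouts as lost to the analysis.
- Dividing by 0.7 instead gives 45 / 0.7 = 64.3, so 65 per arm and 130. That is a separate point, but it means the allowance does not fully cover the loss.

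**2. Children lost at the planned attrition.**

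- 118 × 0.30 = 35.4 lost; 118 × 0.70 = 82.6 remain, about 41 per arm.
- Power of the t-test with 41 per arm at effect size 0.6: 76.5%.

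**3. The analysis over several waves.** The article gives one attrition figure and does not say how loss builds up, so this is a range under assumptions.

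- All 30% lost at one point and no further gaps: about 83 children complete.
- A fresh, independent 30% missing at each of three follow-up waves: 0.7³ = 0.343, and 118 × 0.343 = 40.5. This is an illustrative low end, not an expectation.

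**4. Bias over four visits (simulation).** Assumed: 118 children, correlation 0.8 between adjacent visits and decaying with distance, true mean change −0.30 SD, dropout depending on the previous value, 69% complete at the end.

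| Estimate of mean change | Bias (SD) | Sampling SD |
|---|---|---|
| Complete cases | 0.05 | 0.110 |
| Likelihood, all observed waves | 0.002 | 0.107 |

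The bias made the fall look smaller here; other mechanisms could reverse its sign. The precision gain in this scenario is small, so the main benefit is lower bias.

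**5. The two-visit primary comparison (simulations).** Units are SD of change; the true effect is 0.6.

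| Dropout mechanism | Change-score t-test, bias | Baseline-adjusted, bias |
|---|---|---|
| Completely at random (correlation 0.7 to 0.9) | about 0 | about 0 |
| 40% v 20% by arm only (correlation 0.85) | −0.002 | not needed |
| Related to baseline, equally in both arms (correlation 0.85) | about 0 | not needed |
| About 30%, related to baseline differently by arm (correlation 0.7 to 0.9) | 0.04 to 0.16 | at most 0.006 in size |
| Intervention dropout driven by poor change (correlation 0.85) | −0.213 | −0.197 |

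In the last row 0.197 / 0.213 = 92% of the bias remains after baseline adjustment. Across further scenarios the share was about 86 to 96%.

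**The case against.** The strongest reply is that the article names tests, not a missing-data policy. It never restricts the analysis to complete cases, and an analysis plan could impute before these tests. That stands as a caution: listwise deletion follows from the usual behaviour of the named method, not from a stated rule. It does not remove the point, because the article does fix the ANOVA, and a likelihood model would make better use of the data without relying on an unseen step.

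Several stronger readings are tempting, and the documents do not support them:

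- **That the primary t-test is biased because intervention families carry more burden and may leave more often.** Unequal dropout rates alone give no bias. Dropout must relate to change differently in the two arms.
- **That a mixed model would repair the 10-week result if unsuccessful families leave.** With only baseline observed beforehand, most of that bias remains.
- **That the pooled ANOVA loses the randomised comparison.** It is conditional and within-child, has no arm factor, and is run when controls have also had the program. It has no randomised contrast to lose.
- **That about 40 children will be analysed.** That needs independent 30% loss at three waves, which the article does not say.
- **That every planned ANOVA deletes listwise.** The label used for the secondary outcomes, mixed model ANOVA, is ambiguous and could mean a likelihood model.
- **That children who stop the program are not surveyed.** Section 2.6 ties the post-program survey to 10 weeks and sends surveys by email without limiting them to finishers.

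**Conclusion.** The point holds for the pooled analysis over time. At the planned attrition, classical repeated-measures ANOVA would leave out about 35 of 118 children, and more if losses accumulate, which works against the reason for choosing it. Bias is a risk, not a certainty: it arises if dropout depends on earlier values, and was 0.05 SD against a true change of 0.30 SD in one illustrative scenario. A likelihood model removes it only when missingness depends on observed data.

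For the primary comparison the case is narrower. Baseline adjustment protects against baseline-related dropout that differs by arm (bias of 0.04 to 0.16 SD of change under the assumed models, against about zero after adjustment). It does little against dropout driven by the unobserved 10-week value.

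The sizes rest on assumed correlations and dropout models, and on 30% as the actual loss. The change is worth making before the data are analysed, but the primary analysis is not invalid as it stands.

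**What to change.** 1. **Pooled analysis.** Replace the one-way repeated-measures ANOVA with a likelihood-based linear mixed model (SPSS MIXED) that uses every observed wave. Enter time as categories counted from each child's program start, with an unstructured covariance. Handle the second cohort's waitlist wave explicitly: for example, its first baseline as an additional pre-program time level and the end-of-wait survey as its pre-program value.
2. **Primary comparison.** Analyse children in their assigned arm with a baseline-adjusted model instead of the change-score t-test. A mixed model keeps every randomised child with any observed value. ANCOVA is the simpler alternative, but without imputation it still needs the 10-week value.
3. **Sensitivity analysis.** Add a delta-adjusted multiple imputation of the missing 10-week BMI z-scores, with the range of shifts fixed in advance, to cover dropout related to the unobserved outcome.
4. **Wording.** State whether the mixed model ANOVAs for the secondary outcomes are split-plot ANOVAs or likelihood mixed models.

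The cost is a revision of the analysis text, in the same software and with no new assessments. The downside is a slightly more complex analysis to specify and report.

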The online Better Health Program (BHPO) is a web-based program with health professional coaching sessions for the treatment of childhood overweight or obesity. The BHPO is the online adaptation of the in-person, group-based version, which is an evidence-based, family-centered lifestyle program for primary school aged children aged 7–13 years living with overweight or obesity, which has been successfully delivered and evaluated in Australia for over a decade. The in-person program is consistent with evidence-based guidelines on healthy eating, physical activity, and behavior changes [40]. An RCT evaluating the effectiveness of the face-to-face program demonstrated that it improved the degree of adiposity in children living with overweight or obesity, irrespective of whether families participated once or twice per week [40]. With changes related to the COVID-19 pandemic and digital culture encouraging a shift to e-Health modalities, the BHPO was developed. The web-based program is a 10-week multi-component e-Health program that involves weekly online modules/activity sessions educating on healthy eating, physical activity and behavior changes, weekly individualized phone calls with a health professional coach to support goal setting and program completion, the provision of supporting resources, and access to a closed Facebook group for the sharing of information and social support from other participating families. There has been no evaluation of the program in its online format. 

This protocol paper details the methodology of a study that aims to evaluate the effectiveness of a 10-week e-Health (web-based) healthy lifestyle program for primary-school-aged children aged 7–13 years (referred to hereon as “web-based program”). The primary aim of this study is to evaluate the effectiveness of a web-based program on the participating child’s health outcomes, including the impact of the web-based program on the child’s body mass index z-score (BMI z-score), waist circumference (WC), dietary intake, physical activity, and quality of life post-program-completion (immediately post-program, 6-months, 12-months). This study also aims to explore the experience of families completing a web-based lifestyle program.

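### Beyond 10 weeks, the only firmly planned measure of the program's effect is an ANOVA effect size, which on its ordinary reading shows neither direction nor time point

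*Protocol article*

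**What the plan says.** The aims in the Introduction cover the child's BMI z-score, waist circumference, diet, physical activity and quality of life "post-program-completion (immediately post-program, 6-months, 12-months". Section 2.6 schedules the surveys "at baseline, post-program completion (10 weeks), and 6- and 12-months post-program completion", with one extra set for the control group after its waiting period.

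Section 2.7 makes the primary test an independent t-test to "compare the difference in the mean change in BMI z-score between Cohort 1 and 2 from baseline to 10 weeks". The other firmly planned t-tests and the mixed ANOVAs cover the same 10-week interval.

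For the longer term, the section first explores whether the waitlisted cohort differs from the other over time. It continues "If being waitlisted does not have an impact on the quantitative outcome measures (as anticipated" and then commits to the pooled analysis: "a one-way repeated measures ANOVA will be used to assess the effect size of the web-based program on quantitative outcome measures overtime".

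Two further comparisons are allowed but not promised. The first reads "Independent *t*-tests may also be used to compare the differences in the mean changes in quantitative outcome measures between cohorts", with no time point. The second compares means "for all participants at immediately pre-program (baseline or post-10-weeks waitlisted period) and post-program completion".

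**The concern.** A one-way repeated measures ANOVA on several waves tests whether the wave means differ at all. Its usual effect size summarizes how far those means spread around their average, relative to within-child error. Deviations are squared, so a fall and a rise of equal size count alike, and it makes no difference which wave departs from the others.

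The aim is about direction and timing: whether the outcome has changed after the program, and whether the change is still there at 6 and 12 months. The Introduction and the Discussion both justify the trial by the short-term focus of earlier work, so durability is a main reason for running it. If the planned quantity does not distinguish a lasting reduction from a complete relapse, the secondary analysis does not answer that part of the aim. Any signed contrasts would then be chosen after the data are seen, across five quantitative outcomes and several waves.

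**Working it through.** The plan gives no figure for this analysis, so there is none to reproduce. The check has two parts: what the statistic can distinguish, and whether another planned analysis fills the gap.

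**Inputs**
- From section 2.7: one-way repeated measures ANOVA, with an effect size as the result.
- From section 2.6: waves at pre-program, post-program, 6 months and 12 months.
- Assumed: these four waves are the ANOVA's levels; the index is partial eta squared; the within-child residual SD σ is 0.15 (range 0.10 to 0.20); the mean trajectories are illustrative, in steps of 0.1 z-score.

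**Formula.** Let S be the sum of squared deviations of the four wave means from their average. Per child, the error sum of squares is 3σ², since there are 4 − 1 = 3 degrees of freedom. Then

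partial eta squared = S / (S + 3σ²), and Cohen's f = √(S / 3σ²).

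Both depend on the means only through S.

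**S for four trajectories** (pre, post, 6 m, 12 m)
- Sustained benefit (0, −0.1, −0.1, −0.1): average −0.075; S = 0.075² + 3 × 0.025² = 0.0075.
- Full relapse (0, −0.1, 0, 0): average −0.025; S = 0.075² + 3 × 0.025² = 0.0075.
- Harm (0, +0.1, +0.1, +0.1): average +0.075; S = 0.0075.
- Regain past the start (0, −0.1, 0, +0.1): average 0; S = 0.01 + 0.01 = 0.020.

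**Partial eta squared**

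| σ | 3σ² | Benefit, relapse or harm | Regain past the start |
|---|---|---|---|
| 0.10 | 0.0300 | 0.0075/0.0375 = 0.20 | 0.020/0.050 = 0.40 |
| 0.15 | 0.0675 | 0.0075/0.0750 = 0.10 | 0.020/0.0875 = 0.23 |
| 0.20 | 0.1200 | 0.0075/0.1275 = 0.06 | 0.020/0.140 = 0.14 |

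**Does the result depend on these choices?** Repeat in SD units with a step d = 0.6. The number is borrowed from section 2.3.2 only as a scale. Error per child is 3(1 − r) under equal correlation r between waves.
- Lasting benefit, full relapse by 6 months and lasting harm all give S = 0.75d² = 0.27. At r = 0.8 the index is 0.27/(0.27 + 0.60) = 0.310; at r = 0.5 it is 0.27/(0.27 + 1.50) = 0.153. Under AR(1) correlation of 0.8 it is 0.230. The three patterns tie in every case.
- Other shapes do not tie, but they are not ranked by benefit either. At r = 0.8, benefit held to 6 months and lost by 12 months (0, −d, −d, 0) gives 0.36/0.96 = 0.375, above lasting benefit. Gradual benefit reaching −d at 12 months gives 0.20/0.80 = 0.250, below full relapse.
- With three levels only (pre, post, 12 months) and r = 0.8, benefit, relapse and harm again tie: 0.24/(0.24 + 0.40) = 0.375.
- Simulation under AR(1) 0.8 with 82 children (118 × 0.7 = 82.6) and 2,000 runs gave mean sample values of 0.237 to 0.241 for the tied patterns, with F about 26.

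In contrast, the signed change from pre-program to 12 months is −0.60, 0.00 and +0.60 SD for lasting benefit, full relapse and lasting harm.

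**Does another planned analysis fill the gap?**
- The firm t-tests and mixed ANOVAs end at 10 weeks.
- The optional between-cohort t-tests name no time point. By 6 and 12 months after the program both cohorts have received it (section 2.2), so a difference there concerns waitlisting, not program benefit.
- The optional all-participant comparison runs to post-program completion. Section 2.6 attaches that term to the 10-week survey; the Introduction uses it to cover 6 and 12 months as well. Its reach is ambiguous.

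**The case against.** The other side has real points.

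- **The index and the levels are inferred.** Section 2.7 says only effect size and lists no waves. This stands, so both are labelled as assumptions here. Cohen's f is equally unsigned, and three levels give the same tie.
- **Signed comparisons are not ruled out.** A reader might infer that the later data can enter nothing except the ANOVA and the waitlist exploration. The text does not support that: the optional t-tests could use them, and on the Introduction's use of the term the pre/post comparison could reach 12 months. They remain optional and of uncertain scope.
- **Wave means would ordinarily be shown.** A reader might infer that the trial will announce a large program effect while children end up heavier. Nothing says that means or follow-up contrasts will be withheld, and a table of means would reveal the direction. What stands is narrower: the quantity named as the size of the program's effect does not itself show direction.
- **Contrasts and intervals are detail for a fuller plan.** Their absence alone would be no finding. But the article does more than stay silent: it names the quantity that is to measure the effect over time, and that quantity fits the aim poorly.
- **The analysis is secondary and conditional.** True, though the plan anticipates that the condition will be met.
- **The numbers are illustrative.** True. The SDs and trajectories are assumed, and the exact tie needs equal one-step changes. Blindness to sign needs neither assumption.

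**Conclusion.** The point holds in limited form. In the case the plan anticipates, the only firmly planned measure of the program's effect over time is an effect size that, on its ordinary reading, has no sign, time point or outcome units. Sustained benefit, full relapse and harm of equal size then share one value: 0.10 at a residual SD of 0.15, with a range of 0.06 to 0.20 for SDs of 0.20 to 0.10. Regain past the starting point scores 0.23, more than double. These values rest on the assumed index, waves, SD and trajectories.

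It would be wrong to infer that the trial's main result is compromised. The primary 10-week comparison is a signed difference in mean change between randomized groups and is untouched. The change is worth making because the 6- and 12-month questions belong to the stated aim and the named statistic does not answer them.

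**What to change.** In section 2.7, replace the effect-size sentence with planned estimates. For each quantitative outcome, report the mean change from pre-program to post-program, to 6 months and to 12 months, in the outcome's own units with 95% CIs, from one repeated-measures model with wave as a factor. Define pre-program as that section already does for its optional comparison: baseline, or the end of the waiting period. Say that any omnibus F or effect size is supplementary and will not be reported as the size of the program's effect.

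Add that changes beyond 10 weeks are within-child changes without a concurrent control and will be described as such; the contrasts do not remove that limitation.

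The cost is two or three sentences. Data collection, sample size and software stay the same.

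### An optional secondary pre/post comparison is assigned an independent t-test although both readings come from the same children; the error is conservative and leaves the primary analysis untouched

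*Protocol article*

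**What the plan says.** Section 2.7 (Data Analysis) sets out the quantitative analyses in this order:

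- **Primary analysis.** An independent t-test to "compare the difference in the mean change in BMI z-score between Cohort 1 and 2 from baseline to 10 weeks". The other quantitative outcomes get the same kind of between-cohort test, and mixed ANOVAs supplement these.
- **Pooled analysis over time.** If waiting turns out to have no impact, "a one-way repeated measures ANOVA will be used to assess the effect size of the web-based program on quantitative outcome measures overtime". The stated reason for this step is a gain in power.
- **Optional further tests.** The last sentence begins "Independent *t*-tests may also be used to compare" and gives two alternative uses. One compares mean changes between the cohorts. The other is to "compare the mean differences in quantitative outcome measures for all participants at immediately pre-program (baseline or post-10-weeks waitlisted period) and post-program completion".

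The point concerns only the second of those optional uses. The article does not mention a paired t-test anywhere.

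**The concern.** An independent t-test assumes that the two sets of values come from unrelated people. In the second optional use they do not. The pre-program value is the baseline reading for Cohort 1 and the reading at the end of the waiting period for Cohort 2. The post-program value is a later reading on the same children. Both cohorts are pooled, so the only contrast left is time within child.

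The test would treat 2N correlated readings as 2N separate children and leave out the covariance between a child's two values. The standard error, confidence interval and p-value would then be wrong for each outcome analysed this way: BMI z-score, waist circumference, diet quality, physical activity and quality of life. Where a child's two readings are positively correlated, as is to be expected, real within-child change would be reported with far less precision than the data hold.

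Two further consequences follow. The section pools the cohorts in order to gain power, and this test gives much of that power away. It could also lead to a different conclusion from the repeated measures ANOVA on the same pooled data, and the section does not say which of the two would take precedence.

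**Working it through.** **The plan's own figure.** The article states no sample size or power for the pre/post comparison. Its only such figure is N = 118 for the primary between-group test. Inputs from section 2.3.2: an effect size that "informed by pilot data was 0.6", 5% significance and 80% power (two-sided assumed, since sidedness is not stated), and "a 30% attrition rate based on previous trials on a similar program". A two-sample t-test needs 45 per group. Then 45 × 1.30 = 58.5, rounded up to 59 per group, or 118 in total. The figure reproduces, and it does not depend on the comparison at issue.

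**Inputs for the check**
- N = 82 children with both readings: 118 × 0.70 = 82.6, taken as 82.
- Two-sided 5% level.
- Within-child correlation rho: not given in the article. Assumed range 0.7 to 0.9, with 0.5 added for type I error.
- Mean change: 0.3 SD of the change score, an illustrative assumption.
- Equal variances before and after the program, an assumption.

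**Step 1: standard errors.** With SD sigma at each time point:
- paired: SE = sigma × sqrt(2(1 - rho)/N)
- independent: SE = sigma × sqrt(2/N)
- ratio, independent to paired: 1/sqrt(1 - rho)

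**Step 2: actual type I error.** On correlated pairs the independent t statistic has an SD of about sqrt(1 - rho), not 1. Its critical value on 2 × 82 - 2 = 162 degrees of freedom is 1.975. The true two-sided error is therefore about 2 × [1 - Phi(1.975/sqrt(1 - rho))]. This gives about 0.5% at rho = 0.5, 0.03% at 0.7, 0.001% at 0.8, and effectively zero at 0.9.

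**Step 3: power.** The standardized shift is 0.3 × sqrt(82) = 2.717. The paired t-test has power 0.766, about 77%, whatever rho is, because the change is expressed in SDs of change. For the independent test, power is about 1 - Phi(1.975/sqrt(1 - rho) - 2.717):
- rho = 0.7: 3.605 - 2.717 = 0.889, giving 18.7%
- rho = 0.8: 4.416 - 2.717 = 1.699, giving 4.5%
- rho = 0.9: 6.245 - 2.717 = 3.528, giving 0.02%

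Simulation of correlated pairs (100,000 runs per value) gave 19.6%, 5.3% and 0.08%, close to the approximation.

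| rho (assumed) | SE inflation | Power, paired | Power, independent |
|---|---|---|---|
| 0.7 | 1.83 | 77% | about 19% |
| 0.8 | 2.24 | 77% | about 5% |
| 0.9 | 3.16 | 77% | under 0.1% |

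**A trap in this calculation.** A standard two-sample power routine, fed the same inputs, returns 32%, 23% and 14%. Those values assume that the two samples really are independent, which is the assumption that fails here. They understate the loss.

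**The case against.** The case for leaving the text alone has real weight:

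- **The test is optional.** The wording permits it and does not commit to it. It comes last in the section and concerns an uncontrolled before/after contrast.
- **A valid method is already planned.** The repeated measures ANOVA respects the pairing, and with two time points it is equivalent to a paired t-test. This stands in part: the ANOVA is conditional on waiting having no impact, so it does not always cover the gap.
- **The error is conservative.** With positive correlation it cannot manufacture a benefit. It can only hide or blur a real change. This stands in full.

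One might also read the second use as a between-cohort comparison, for which the independent test would be right. The text does not allow this. It refers to all participants, defines the pre-program point separately for the two cohorts so that they can be pooled, and names pre- and post-program as the two things compared.

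In the other direction, a reader might infer that the trial's main result is compromised, or that the plan risks false-positive claims. The article supports neither. The primary test compares change scores between two randomized groups of different children, for which an independent t-test is appropriate as regards pairing. The randomized secondary comparisons and the sample size are likewise untouched.

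**Conclusion.** The text is wrong as written, for one optional secondary comparison. An independent t-test on pooled pre- and post-program values ignores the pairing. Its standard error is too large by a factor of 1.8 to 3.2 over an assumed correlation of 0.7 to 0.9, and in the illustrated case most or nearly all of the power is lost.

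The defect itself and the direction of the error need only a positive within-child correlation. The sizes rest on assumptions that the article does not supply: the correlation, equal variances at the two time points, 82 complete pairs, and the illustrative change of 0.3 SD of change.

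Severity is minor to moderate. The sentence should be corrected because it names an unsuitable test for a specified comparison and undercuts the stated reason for pooling. It gives no ground for doubting the primary analysis.

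**What to change.** Amend the last sentence of the quantitative part of section 2.7:

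- For the pooled comparison of pre-program with post-program values, replace the independent t-test with a paired t-test or an equivalent within-child model.
- Report the mean within-child change with its 95% CI.
- Keep independent t-tests for between-cohort contrasts only.

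The cost is one sentence. No new data, no change in sample size and no change to the primary analysis are needed.
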